# A prospective, double-blind, randomized, controlled clinical trial comparing standard wound care with adjunctive hyperbaric oxygen therapy (HBOT) to standard wound care only for the treatment of chronic, non-healing ulcers of the lower limb in patients with diabetes mellitus: a study protocol

**DOI:** 10.1186/1745-6215-12-69

**Published:** 2011-03-07

## Abstract

**Background:**

It has been suggested that the use of adjunctive hyperbaric oxygen therapy improves the healing of diabetic foot ulcers, and decreases the risk of lower extremity amputations. A limited number of studies have used a double blind approach to evaluate the efficacy of hyperbaric oxygen therapy in the treatment of diabetic ulcers. The primary aim of this study is to assess the efficacy of hyperbaric oxygen therapy plus standard wound care compared with standard wound care alone in preventing the need for major amputation in patients with diabetes mellitus and chronic ulcers of the lower limb.

**Methods/Design:**

One hundred and eighteen (59 patients per arm) patients with non-healing diabetic ulcers of the lower limb, referred to the Judy Dan Research and Treatment Centre are being recruited if they are at least 18 years of age, have either Type 1 or 2 diabetes with a Wagner grading of foot lesions 2, 3 or 4 on lower limb not healing for at least 4 weeks. Patients receive hyperbaric oxygen therapy every day for 6 weeks during the treatment phase and are provided ongoing wound care and weekly assessments. Patients are required to return to the study centre every week for an additional 6 weeks of follow-up for wound evaluation and management. The primary outcome is freedom from having, or meeting the criteria for, a major amputation (below knee amputation, or metatarsal level) up to 12 weeks after randomization. The decision to amputate is made by a vascular surgeon. Other outcomes include wound healing, effectiveness, safety, healthcare resource utilization, quality of life, and cost-effectiveness. The study will run for a total of about 3 years.

**Discussion:**

The results of this study will provide detailed information on the efficacy of hyperbaric oxygen therapy for the treatment of non-healing ulcers of the lower limb. This will be the first double-blind randomized controlled trial for this health technology which evaluates the efficacy of hyperbaric oxygen therapy in prevention of amputations in diabetic patients.

**Trial registration:**

ClinicalTrials.gov Identifier: NCT00621608

## Background

Non-healing foot ulcers and their sequelae are a major source of morbidity and resource use for patients with diabetes mellitus [1-4]. Peripheral neuropathy, peripheral vascular disease, and poor glycemic control, in conjunction with minor foot trauma, increase the likelihood that patients with diabetes will develop foot ulcers. Because of the neuropathy, a foot injury and subsequent infection cannot be felt and since circulation is also affected, wound healing is compromised and causes the original ulcer to become chronic and may eventually require amputation [5-7]. For those patients with ulcers, excess healthcare costs are substantial. Ramsey et al [8] found that the attributable cost for a 40- to 65-year-old male with a new foot ulcer was $27,987 USD for the 2 years after diagnosis. Not surprisingly, quality of life is significantly reduced in patients with ulcers and after major amputations [9].

In patients with diabetes, it is estimated that the annual incidence of foot ulcers varies from 1.2 to 3.0% [8,10] and the rate of lower extremity amputation (LEA) has been measured to range between 6% and 23.5% [11]. Major LEAs are amputations of the leg above or below the knee, whereas minor LEAs involve amputation of the toes or the forefoot [12]. The incidence of major amputation in a study of 8,905 patients with diabetes in the United States was found to be 0.9% [8]. Additionally, a significant proportion of these amputees undergo further amputations of the same or other limb [8,11,13,14].

The standard of care for treating diabetic foot ulcers includes the maintenance of optimal blood glucose levels; use of debridement, antibacterials, and dressings; administration of antibiotics to control infection; adequate nutrition; pressure relief in the areas of the foot that are most subject to weight bearing; and amputation. There has also been increasing interest in the use of hyperbaric oxygen therapy (HBOT) as an adjunctive treatment for diabetic ulcers. It has been suggested that the use of adjunctive HBOT will improve the healing of diabetic lower leg ulcers, and decrease the risk of LEA [15-20].

HBOT is an established technology that has been in use for more than 40 years. For wound healing treatment, a person is placed in a compression chamber under pressure greater than one atmosphere absolute (ATA) of 100% oxygen. The pressure increases the level of oxygen dissolved in the blood plasma affecting the immune system, wound healing, and vascular tone [21]. Treatment regimens vary from 90-120 minutes once or twice daily for approximately 30 sessions [22]. Complications associated with HBOT are infrequent but may include claustrophobia; ear, sinus or lung damage due to the pressure; temporary worsening of short sightedness, rarely is permanent; and oxygen poisoning [23]. Careful monitoring during the treatment sessions and follow-up by a trained health care provider is recommended.

There is evidence to support that adjunctive HBOT is more effective in the treatment of chronic diabetic foot ulcers than standard care alone. However, this evidence of efficacy for chronic diabetic foot ulcers is limited. In particular, several, very small, prospective, randomized, controlled trials can be identified in the published literature to date [16,17,19]. The first trial [17] randomized 30 patients, the second randomized 68 patients [16]. Only two double blind placebo controlled trials have ever been reported including a trial conducted in 2003 which randomized just 16 patients [19], while the more recent largest trial to date successfully randomized and completed 37 patients in each arm [24]. In this latest study, the primary outcome was healing of the index wound, however, the healing rate in the control group in this study was very low at 29%. All trials demonstrated that more wounds healed in HBOT-treated patients compared to the control group. Two of the three studies [16,17] demonstrated a reduction of major LEA in the HBOT group, while the other study showed no difference between the groups. In addition, successes of adjunct HBOT for the treatment of diabetic foot ulcers have been reported in a few small case series and retrospective or prospective cohorts [15,18,25-28]. However, many of these originated from one clinical centre [16,18,27,28].

Using this limited evidence, several health technology assessments and systematic literature reviews have been conducted that suggested that adjunctive HBOT for diabetic foot ulcers is more effective than standard care alone [29-37]. At the same time, all reports recommend that good quality studies are required to confirm the comparative benefits of the technology for chronic diabetic foot ulcers in order to help clinicians and policy-makers decide whether HBOT should be more widely utilized [33,34,37].

Currently in Ontario, HBOT is an accepted treatment for chronic diabetic ulcers and physicians who provide this service are reimbursed under the current Ontario Health Insurance Plan (OHIP) payment schedule. However there are only a few facilities which provide comprehensive wound care and adjunctive HBOT.

A recent review of the HBOT literature concluded that the quality of the evidence assessing the efficacy of HBOT as an adjunct to standard therapy for people with non-healing diabetic foot ulcers is low, and the results are inconsistent [32]. Thus, the goal of the current study is to conduct a well-designed, double-blind randomized controlled trial that would provide quality efficacy data on the use of adjunctive HBOT for the prevention of major limb amputations for patients with moderate and severe chronic diabetic foot ulcers. To better assess the place of HBOT in modern wound care, the best practice principles of treating chronic diabetic foot ulcers are applied in both control and treatment arms.

This study was initiated based on a recommendation by the Ontario Health Technology Advisory Committee that stated that a "well designed, adequately powered, clinical trial be undertaken to provide evidence on which to make a definitive decision on the effectiveness of HBOT in the treatment of non-healing diabetic foot ulcers".

### Objectives

#### Primary Objective

This study is intended to assess the efficacy of HBOT plus standard wound care compared with standard wound care alone in preventing the need for major amputation in patients with diabetes (Type 1 or 2) with moderate to severe chronic wounds of lower limbs (Wagner scale 2 to 4) [38].

#### Secondary Objectives

Further objectives of the study are to determine if HBOT, in combination with standard wound care, significantly improves the healing of chronic ulcers compared with standard wound care alone through the assessment of wound measurements and wound closure. The safety, amount of health care resource utilization, health-related quality of life (HRQL), and cost-effectiveness of HBOT will also be measured.

### Hypothesis

HBOT plus standard wound care is more effective than standard wound care alone at preventing the need for major amputation (metatarsal and up) in patients with diabetes with moderate to severe chronic wounds of lower limbs.

## Methods/Design

### Design

Patients are randomised either to receive standard wound care alone or HBOT in combination with standard wound care for the treatment of chronic lower limb ulcers in patients with diabetes (Figure 1).

**Figure 1 F1:**
[figure not shown]
**Study Schema**.

### Setting and participants

This study is being conducted at the Judy Dan Wound Care and Research Centre an University Health Network Research affiliated wound care facility. Patients with non-healing diabetic lower limb ulcers are referred by physicians and also identified through a number of wound care clinics in the Greater Toronto Area (GTA) as well as from regional Community Care Access Centres.

### Inclusion Criteria

1) Age ≥ 18 years; 2) Type 1 or 2 Diabetes Mellitus; and 3) Wagner grading [38] of foot lesions 2,3 or 4 on lower limb not healing for at least 4 weeks.

### Exclusion Criteria

1) Impending urgent amputation due to ongoing or exacerbated infection; 2) exposed calcaneus bone with no prospect of weight bearing potential even if defect has been healed; 3) any of the following medical conditions which preclude safe treatment in a monoplace chamber: clinical depression; severe dementia; claustrophobia; seizure disorder; active asthma; severe chronic obstructive pulmonary disease; previous thoracic surgery; previous spontaneous or trauma induced pneumothorax; history of severe congestive heart failure with left ventricular ejection fraction less than 20%; unstable angina; chronic sinusitis; chronic or acute otitis media or major ear drum trauma; severe kyphoscoliosis; severe arthritis; or morbid obesity; 4) history of chemotherapy with use of Bleomycin; 5) participation in another investigative drug or device trial currently or within the last 30 days; 6) current candidates for vascular surgery, angioplasty or stenting; 7) major large vessel disease; 8) undergone vascular surgery or angioplasty within the last 3 months; 9) women who are currently pregnant or are breast feeding or women of childbearing potential who are not currently taking adequate birth control.

### Sample Size

A comprehensive search and review of the electronic medical literature databases was conducted to identify randomized controlled trials of HBOT versus standard treatment to collect data to calculate the sample size required for the current study. Sample size calculations were to be based on evidence from published randomized controlled trials comparing the efficacy, in terms of rates of major amputation, of HBOT versus standard treatment for patients with various wound classifications using the Wagner's Ulcer Classification Grade [38].

Of the 348 citations obtained, only one study [16,19] reported the rates of major amputation for Wagner's classifications necessary for the calculation of sample size for this study given that it was decided a priori that patients with Wagner Grades of 2,3 or 4 would be recruited into the study. Based on these data, the expected event rate in the standard care group was 39.29% and 11.54% in the HBOT group and using a two-sided test for equality.

Using these data, it was estimated that a total of 94 patients were needed for this study (47 patients per treatment group). However, due to the fact that subjects might leave the study for a variety of reasons (e.g. loss to follow-up, non-compliance with treatment, or death), the sample size was adjusted to accommodate for this. It was assumed that there was a likely dropout rate of 20%. This assumption would require a total of 118 subjects, or 59 subjects in each treatment group (i.e., 94/(1-0.20) = 118).

### Recruitment of patients

Two streams of referrals are utilized:

1. Patients referred by primary care physicians undergo full assessment, including assessment by the participating vascular surgeon and a foot care specialist to determine best treatment options for the patient. Once it has been determined that they are not candidates for surgical/angioplasty/stenting and they fulfill inclusion criteria they are asked to participate in the trial.

2. Patients referred by specialists, most commonly vascular and plastic surgeons, usually have already undergone detailed assessment and their wounds deemed not amenable by interventional techniques. Previous test results are forwarded to the participating vascular surgeon to examine whether a sufficient level of assessment has been performed, and whether inclusion/exclusion criteria are met, the patients are then asked to participate in the study.

### Randomisation and Blinding

Patients are randomized using a computerized block randomization schedule with a multiple block size of four. The unblinded HBOT technician obtains the treatment allocation through an internet-based automated randomization system. Researchers and patients are blinded to treatment allocation; the only unblinded individual is the technician responsible for controlling the hyperbaric oxygen chamber.

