### Data collection

Data to evaluate the efficacy of HBOT are collected at screening, baseline, and weekly throughout the 6-week treatment phase, weekly throughout the 6-week follow-up phase at 30 and 52 weeks. At the end of the 6-week follow-up phase (i.e. week 12), the patient is sent to the participating vascular surgeon for an amputation evaluation. If the patient's wound has not healed, the wound care physician, in consultation with the vascular surgeon will then decide if further HBOT or other treatment is indicated. Once all study data for each patient are received, the randomization assignment may be revealed. Data are collected via interview, self administrated questionnaire, physical and biological measurements. Data collection instruments and the study timeline are summarized in Table 1. All instruments used have been previously validated.

**Table 1 T1:** Schedule of study assessments and evaluations

			Treatment Phase		Follow-up Phase		Long-Term Follow-up	
			
Clinical Assessments, Testing and Investigations	Screening and Randomization	Baseline	Weeks 1 to 6	End of Treatment	Weeks 6 to 12	End of Follow-up	Week 30	Week 52
Suitability for HBOT	X							

Electrocardiogram	O							

Pulmonary Function Testing	O	X						

Audiogram	O							

Chest X-ray	O							

X-ray of affected limb	O	X						

Nuclear bone scan	O							

Vascular Exam	X	O	O	O	O	X		

History & Physical		X						

Demographics		X						

Treatment Details		X	X					

Wound Classifications (Wagner, Bates)	X	X	X		X			

Wound Measurements		X	X		X			

Wound Characteristics		X	X		X			

Digital Photograph of wound		X	X		X			

Dressing Changes	X	X	X		O	O		

Concomitant Meds		X	X		X			

Assess for Infection	X	X	X		X			

Mobility Status		X	X		X			

Adverse Events		X	X		X		X	X

Outcome Assessment	X	X	X		X			

Unblinding		O	O	O	O	O		

Laboratories	X	X		X		X		

Resource Utilization		X	X		X		X	X

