## Disscussion

This study has been designed to address some of the shortcomings of previous research, namely this study will be the largest and first double-blind randomised controlled trial to evaluate the efficacy of HBOT for the prevention of major amputations in diabetic patients with non-healing ulcers of the lower limb. The study uses a remote randomization system to protect concealment of allocation and proposes that the primary comparative analyses be conducted on an intention-to-treat basis in accordance with the 2010 CONSORT statement [40].

Participants are followed up for a 12-month period in order to capture the impact of HBOT treatment in both the immediate (i.e. 12 weeks) and longer term. This two-arm study, with 49 participants per group, should provide sufficient power to detect a meaningful difference in amputation. If successful, this intervention may lead to substantial and important changes in the management of diabetes patients at risk of amputation due to non-healing ulcers of the lower limb.

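### Four is the only block size named, and it was published during recruitment at one centre. Combined with patient-by-patient reveals, it could disclose the arms of block-mates not yet assessed (minor).

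*Protocol article*

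**What the plan says.** Randomisation and Blinding specifies a "computerized block randomization schedule with a multiple block size of four" and names no other size. It continues: "The unblinded HBOT technician obtains the treatment allocation through an internet-based automated randomization system". Researchers and patients are blinded, and "the only unblinded individual is the technician responsible for controlling the hyperbaric oxygen chamber".

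There is one centre (Setting and participants: "This study is being conducted at the Judy Dan Wound Care and Research Centre"). The abstract says that patients "are being recruited if they are at least 18 years of age", so the block size became public while patients were still being entered. Sample Size gives the total: "This assumption would require a total of 118 subjects, or 59 subjects in each treatment group".

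Data collection describes the week-12 referral to the vascular surgeon and the decision on further treatment for unhealed wounds. It then adds: "Once all study data for each patient are received, the randomization assignment may be revealed". The same section also lists data collection at weeks 30 and 52, so the time at which a patient's data count as complete can be read in two ways. Table 1 has an optional unblinding row running from baseline to the end of follow-up.

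The Discussion says: "The study uses a remote randomization system to protect concealment of allocation".

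**The concern.** A remote system hides the next assignment from view. It does not stop anyone from working it out when the block length is known and the earlier assignments in the block are known too. With short blocks of one known length, some assignments follow with certainty.

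Two things could be at stake. One is concealment: someone able to predict the next arm could influence who is entered and when. The other is blinding: staff who learn some patients' arms could deduce the arms of block-mates still being assessed. The second matters here because the primary outcome includes meeting criteria for major amputation, as decided by a vascular surgeon. Some of those criteria, such as disabling pain or continuing risk of systemic infection, call for judgement.

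**Working it through.** **Inputs.** Block size 4 (Randomisation and Blinding); two arms at 1:1 and 118 patients (Sample Size, where 94/0.80 = 117.5, rounded up to 118); one centre. No strata are mentioned, so a single list is assumed. The article gives no predictability figure to reproduce.

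**Certain allocations, blocks of four.** A block with two patients per arm has 6 possible orderings.
- Positions 1 and 2 are never certain.
- Position 3 is certain when the first two are in the same arm: 2 of 6 orderings, or 1/3.
- Position 4 is always certain.

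The expected number per block is 1/3 + 1 = 4/3, which is (4/3)/4 = 33.3% of allocations. Over 118 patients (29 full blocks and 2 further patients) it is 29 × 4/3 = 38.7, or 32.8%.

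**Best guess, blocks of four.** The success probabilities by position are 1/2, 2/3, 2/3 and 1. Position 3 is 1/3 × 1 + 2/3 × 1/2 = 2/3. The mean is (17/6)/4 = 17/24 = 70.8%, against 50% by chance.

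**Other block schemes.** These come from 1,000 simulated lists of 118, with an observer who knows the set of possible sizes and all earlier allocations, but not the size of each block.

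| Scheme | Certain | Best guess correct |
|---|---|---|
| Fixed 4 (exact) | 33.3% | 70.8% |
| Random 4, 8 | 7.4% | 67.8% |
| Random 4, 6, 8 | 2.2% | 67.9% |

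If multiple means varying multiples of four, the 4, 8 row is the relevant one. Were each block's size also known, that scheme would give 24%.

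**Timing.** The article does not state the accrual period. I assume 24 to 36 months: the upper end is the whole study duration of about 3 years, and the lower end allows a year for follow-up.
- Accrual is 118/24 = 4.92 to 118/36 = 3.28 patients per month.
- A block fills in 4/4.92 × 52/12 = 3.5 weeks to 4/3.28 × 52/12 = 5.3 weeks.
- The average gap between entries is a quarter of that: 0.9 to 1.3 weeks.

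*Effect on enrolment.* The fourth patient enters about three gaps (2.6 to 4.0 weeks) after the first. A reveal at week 12 or later therefore comes after the block has filled, and cannot predict that block's next entry.

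*Effect on blinding, reveals at week 12 in order of entry.* When the third patient is revealed, the fourth is one gap (0.9 to 1.3 weeks) from the week-12 evaluation, and that arm is now known. When the first two are in the same arm (1/3 of blocks), the third and fourth are known one and two gaps ahead (up to 1.8 to 2.6 weeks). The count is again 4/3 patients per block, or one third.

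*Effect on blinding, reveals after week 52.* All block-mates are well past week 12. Only late data (EQ-5D, adverse events, resource use at week 52) could be affected.

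**The case against.** A reader might infer that enrolment concealment has failed. The documents do not support that. Prediction needs the earlier allocations in the same block, and only the technician is stated to have them. Eligibility is assessed by others (Recruitment of patients), and no part in screening, consent or timing is described for the technician. A condensed article need not spell out that separation, so its absence is no finding. Nor does block size affect blinding through the technician, who already knows every treated patient's arm. As shown above, the individual reveals come too late to help anyone steer entry into the same block. All of this stands.

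It is also fair that fixed is a reading and not the article's word; that the number of patients still to be entered after publication is unknown, so 39 of 118 describes the whole trial and not what an amendment could change; and that varying the sizes barely lowers the best-guess rate.

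The last argument is that an early reveal discloses arms directly and is a blinding matter whatever the block size. That is only partly right. A reveal directly discloses the arm of a patient whose data are in. Short blocks of known length extend it to patients whose data are not.

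**Conclusion.** The point holds as a minor one. On the natural reading, repeated blocks of four, one third of allocations follow with certainty from the earlier ones in the block. On the alternative reading, a hidden mix of 4 and 8, about 7% do.

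The exposure that the documents support is to blinding, and it is conditional: reveals must happen at about week 12, in roughly the order of entry, to staff who know the block size and the order of entry. The arm of a block-mate could then be deduced about one to two and a half weeks before that patient's amputation evaluation. If reveals wait for week-52 data, the primary outcome is not exposed by this route. The timing rests on the assumed 24 to 36 months of accrual.

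**What to change.** 1. Clarify in Randomisation and Blinding whether all blocks have four patients or whether sizes vary.
2. For the remaining allocations, have the internet system draw block sizes at random, for example from 4, 6 and 8. Withhold the sizes from site staff and from publications until database lock.
3. State in Data collection that individual assignments are not revealed before database lock, except for safety.

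The third change closes the reveal route for everything but safety unblinding. The second limits what can be deduced from any allocation that does become known: certain allocations fall from 33% to about 2% (2.2% of 118 is 2 to 3 patients over a full list), while the best guess moves only from about 71% to 68%. The gain is the removal of certainty.

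The cost is a configuration change and a short amendment. The final imbalance between arms could reach four patients if the last block has size 8 and stops halfway, with negligible loss of power; the sample size does not depend on the block size. The reveal sentence follows directly on the week-12 decision about further treatment, so the investigators must settle how deferral fits with that decision. That is a clinical matter on which this point takes no position.
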